#### Secondary Outcome Variable

The cumulative combined D_12_FS increment (Table 2) is a variant of the primary outcome measure that adds transitions to and from non-cavitated caries (i.e., D_1_, PD_1_, FD_1_, CD_1_). This measure is constructed by scoring transitions toward worsening oral health as positive, biologically plausible "reversals" (i.e., remineralization indicated by transition from D_1 _to S) as negative, and no change or implausible/impossible as zero, and then summing over all surfaces examined. Thus, this measure can take negative values. A maximum weight of 2 is assigned to transitions observed between a pair of consecutive examinations that could theoretically be observed as intermediate steps (each contributing an increment) over two to three years of follow-up, so that the cumulative increment could not be greater than any single change. For example, an increment from S to D_2 _is given greater weight on the assumption that it should add the same increment to the cumulative score as two transitions (S to D_1_, then D_1 _to D_2_).

**Table 2 T2:** Combined D_12_FS increment: Scoring weight of transitions in tooth surface for secondary outcome variable.

		**T**_**1**_**: Second call**										
**T**_**0**_**:** **First** **Call**		**S [P]**	**D**_**1 **_**[PD**_**1**_**]**	**D**_**2 **_**[D**_**3 **_**PD**_**2 **_**PD**_**3**_**]**	**F**	**FD**_**1**_	**FD**_**2 **_**[FD**_**3**_**]**	**C**	**CD**_**1**_	**CD**_**2 **_**[CD**_**3**_**]**	**Y**	**M**
	
	**S [P]**	0	1	2	2	2	2	0	0	0	0	0
	
	**D_1 _[PD_1_]**	-1	0	1	1	1	1	1	1	1	0	0
	
	**D_2 _[D_3 _PD_2 _PD_3_]**	**-2**	**-1**	0	0	1	0	0	0	0	0	0
	
	**F**	**-2**	**-1**	**0**	0	1	2	0	1	2	0	0
	
	**FD_1_**	**-2**	**-2**	**-1**	-1	0	1	1	1	1	0	0
	
	**FD_2 _[FD_3_]**	**-2**	**-2**	**-2**	0	**-1**	0	0	0	0	0	0
	
	**C**	**-2**	**-1**	**0**	0	1	2	0	1	2	0	0
	
	**CD_1_**	**-2**	**-2**	**-1**	-1	0	1	-1	0	1	0	0
	
	**CD_2 _[CD_3_]**	**-2**	**-2**	**-2**	**-2**	**-1**	0	0	**-1**	0	0	0
	
	**Y**	0	0	0	0	0	0	0	0	0	0	0
	
	**M**	0	0	0	0	0	0	0	0	0	0	0

S = sound

P = pit and fissure sealant

D_1 _= non-cavitated caries lesion

D_2 _= cavitated enamel caries lesion

D_3 _= caries lesion penetrating into dentin

F = filled

C = crowned

#### Other Study Measures

In addition to the caries examination data, other study data are collected periodically to assist in monitoring participant safety and as measures of risk factors and other mediators of caries incidence. Additional data collected at baseline describe participants' demographic characteristics, self-reported oral hygiene behaviors, fluoride exposure, and exposure to antibiotics. Adherence is measured by self- reported lozenge use at each visit and by the cumulative bottles of lozenges used during the study. Staff also query participants as to receipt of preventive dental care and use of over-the-counter preventive agents since the last contact. Forms used for all data collection are available on the study's public website at http://www.xactstudy.org.

#### Safety Monitoring

A medical history checklist was collected at baseline, and is updated at each subsequent examination visit. Also at every examination visit, participants respond to questions about side effects and possible serious adverse events. Participants are also queried regarding side effects at all between examination telephone calls.

### Quality Control

All clinical center staff were centrally trained and certified in all necessary aspects of study operations, including questionnaire administration and data entry. Initial training occurred prior to the start of randomization, with recertification occurring about annually. The data coordinating center monitors study progress on an ongoing basis and generates regular trial monitoring reports for review by the study's Steering Committee and the Data Safety Monitoring Board (DSMB). The Data Coordinating Center uses a secure, web-based application for data entry and management. This application incorporates real-time error checking and quality assurance at the time of data entry and prompts clinical center staff about potentially erroneous data during data entry. Additional "back-end" checks are performed at the data coordinating center. The data coordinating center maintains an electronic audit trail of all errors and error resolutions. Finally, the DCC conducts annual site visits at each clinical center to check whether data collection, recording, and entry meet standards for quality assurance as defined in Good Clinical Practice (GCP) [15].

### Sample Size

We based our required sample size on a series of large longitudinal cohort studies that permitted estimates of expected combined net D_2_FS increment in the placebo group of the trial. These studies, reviewed by Griffin et al. [16] and Thomson [1] did not include measurement of D_1 _lesions. Although they varied in design, these studies reported sufficient data to calculate reasonable values for three-year untreated incidence rates of root, coronal, and total caries, under the assumption of constant rates over years. These estimated surface increments were 1.4, 2.5 and 3.7 respectively. We estimated the sample size needed, using a range of values (2.3 to 4.9) for the placebo cumulative, combined D_2_FS increment over three years, and assuming that the treatment might result in a 20% reduction, with power set at 80% and one-sided alpha at 0.025. Using PASS 2005 with a Poisson regression model and a large, but plausible overdispersion parameter (3.0, to account for excess variability), and assuming attrition of 10% per year, we obtained a sample size target of 250 at each clinical site (750 total).

### Analysis

#### Missing Data

We expect to have complete data on baseline measures, so missing data are likely to arise only with respect to the annual and final examination visits. Since our analysis approach accounts for time at risk, the primary outcome of combined D_2_FS increment will be imputed from baseline to year 1 only for participants who failed to return for any annual visits, and the time-at-risk will be defined as the target date for the first annual visit. We will use an inclusive model to improve the likelihood of unbiased imputed values [17]. We will multiply impute missing data using data augmentation with Markov Chain Monte Carlo sampling. Five to eight versions of the final analysis dataset will be created and analyzed using identical procedure, followed by combining the results so that variation between imputation versions is incorporated in the standard error and p-value.

#### Primary Outcome Analysis

The primary analyses will be an intent-to-treat (ITT) analysis, on a sample that includes all randomized patients and classifies them according to their assigned treatment group, regardless of their adherence to the protocol. The primary outcome will be analyzed in a negative binomial regression model (using SAS^® ^PROC GENMOD) in which treatment group and clinical center indicators are included as fixed categorical design factors. Planned (*a priori*) covariates are age and age-squared, intensity of preventive regimen, oral hygiene behavior measures, and severity of baseline caries, which is defined as the sum of decayed surfaces at the baseline examination. We will include the natural log of person-years at risk, ln(*t *_i_), as an offset to adjust for length of time since the participant was randomized. Formally, the model is,

ln(μi)=β0 +  Tiβ1+ S1β2 + S2β3 + ci'γ + ln(ti),

or equivalently,

ln(μi/ti) = β0 + Tiβ1 + S1β2 + S2β3++ ci'γ,

where *μ *is the mean observed increment, *μ */t is the incidence of new progressions per year, T is the treatment indicator (0 = placebo, 1 = xylitol), S_1_, S_2 _are clinical site indicators, **c**_i _represents a vector of covariates, and **β **and **γ **represent vectors of parameters to be estimated. The resulting *β*_1 _coefficient thus has the interpretation of the ln(relative risk) for progression for the xylitol compared to placebo lozenges, and the null hypothesis test of no difference between treatment arms is a test of H_0_: *β*_1 _= 0 vs. the alternative hypothesis H_1_: *β*_1 _< 0. The actual fraction of a year's exposure to the lozenges will be used where known, otherwise, the offset will be set to the midpoint of the period between the first examination missed and the last examination attended. In secondary analyses of the primary outcome, we will conduct sensitivity analyses by applying the alternative distributional models (Poisson, mixture models) mentioned above to the same data.

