## Background

Dental caries is a significant problem for adults. Despite a widely held perception that caries is a disease of childhood, it has become clear that the incidence of new lesions in adults is approximately the same as the incidence in adolescents [1]. Dentistry has been slow to recognize and address this problem. Specifically, caries preventive procedures have been infrequently provided to adults in the past [2], although a recent report does suggest that dentists are now more likely to provide such procedures if they identify an adult patient as "caries active"[3].

While it is likely that there are several reasons for the dental profession's inattention to the prevention of caries in adults, lack of evidence about the effectiveness of preventive treatments in adults may be an important factor. Presumably, this lack of evidence contributes to practitioners' reluctance to provide preventive treatment to adults, and may limit purchasers' enthusiasm for coverage for such treatment. The National Institutes of Health Consensus Development Conference on Diagnosis and Management of Dental Caries Throughout Life noted that virtually all of the dental profession's knowledge concerning the effectiveness of caries preventive interventions had come from trials in children and adolescents [4]. The Conference recommended additional caries trials in adults.

In response to that recommendation we designed a randomized clinical trial, the Xylitol for Adult Caries Trial (X-ACT), to test the hypothesis that use of xylitol lozenges will reduce dental caries incidence in caries-active adults. At the time that the trial was designed, three reviews of the effectiveness of xylitol had appeared [5-7]. Although each review found evidence for a xylitol preventive effect, two reviews indicated that the available evidence was not strong enough to permit a firm conclusion of therapeutic effectiveness. All of the reviews indicated that the existing evidence needed to be supplemented by well-designed trials. Because xylitol is already approved as an over-the-counter sweetener, the intervention could be delivered outside the context of a dental office, thus making wide dissemination and implementation feasible. In addition, delivery through candy, gum, or lozenges (mints) would be likely to promote adherence to the preventive regimen. This paper describes the X-ACT protocol.

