### Randomization and Treatment Contacts

Those enrollees who completed the run-in period with adequate self-reported adherence (consumption of more than half of lozenges scheduled during the run-in period) and who indicated a willingness to participate in the full trial attended a baseline visit wherein eligibility criteria were confirmed, and a caries examination was performed. Eligible enrollees were randomized to either the active or placebo arm, additional information was collected, and the initial supply of lozenges was dispensed. Randomization was carried out using a web-based randomization application process. Allocation assignments were stratified by site and age group (≥ 50, < 50 yrs.) in permuted blocks of varying sizes within each stratum. Staff and participants were blinded to treatment assignment. A total of 691 participants were randomized, 92% of the goal of 750.

In the periods between the visits for caries examinations, participants are contacted by telephone on a quarterly basis to assess adherence, side effects, receipt of preventive dental care; to screen for possible serious adverse events; and to arrange for re-supply of lozenges. Participants are asked how many unopened bottles they have on hand, and sufficient bottles for the next three months are dispensed from the participant's master supply at the clinical site and are delivered by courier.

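### The primary model adjusts for intensity of preventive care without tying it to baseline, and the protocol describes collecting preventive care only after randomization

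*Protocol article*

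**What the plan says.** In the protocol article, Primary Outcome Analysis promises an intent-to-treat analysis that "classifies them according to their assigned treatment group, regardless of their adherence to the protocol". The model is a negative binomial regression with treatment, clinical center and a list of a priori covariates: "covariates are age and age-squared, intensity of preventive regimen, oral hygiene behavior measures, and severity of baseline caries". Of these, caries severity alone carries a time point, in the clause "which is defined as the sum of decayed surfaces at the baseline examination".

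Other Study Measures describes two kinds of data:

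- At baseline: "Additional data collected at baseline describe participants' demographic characteristics, self-reported oral hygiene behaviors, fluoride exposure, and exposure to antibiotics".
- During the study: "Staff also query participants as to receipt of preventive dental care and use of over-the-counter preventive agents since the last contact".

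The same section says these measures serve safety monitoring and act as risk factors or mediators of caries. Randomization and Treatment Contacts gives the timing of the second kind: between examinations, participants are "contacted by telephone on a quarterly basis to assess adherence, side effects, receipt of preventive dental care".

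**The concern.** The preventive-regimen covariate has no stated time point. Preventive dental care is not in the baseline list, and the places that describe collecting it put it after randomization. An analyst who follows the article could well build the covariate from follow-up data.

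The Background supplies a reason why that would matter. It cites a report suggesting that dentists are "more likely to provide such procedures if they identify an adult patient as" caries active. If xylitol works, the placebo arm forms more lesions and may then receive more preventive care. Follow-up care would then partly be a result of the outcome. Holding it constant compares xylitol and placebo participants with similar care, and therefore with more similar caries experience than randomization gave them. Part of the treatment effect is removed from the estimate that the primary test rests on.

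**Working it through.** **Time point of each covariate**

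| Covariate in the primary model | Time point in Primary Outcome Analysis | Where collection is described |
|---|---|---|
| Age, age-squared | not needed | demographics at baseline |
| Caries severity | baseline examination | baseline examination |
| Oral hygiene behaviors | none given | baseline list only |
| Intensity of preventive regimen | none given | baseline list has fluoride exposure; preventive care and over-the-counter agents appear only at later contacts |

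Hygiene has one described source, at baseline. The preventive term has a possible baseline source (fluoride exposure) and a closer match in the follow-up data.

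**The plan's own figure.** The concern does not depend on the sample size, but reproducing it shows that the planning inputs are read correctly. Inputs from Sample Size: placebo three-year increment μ = 3.7, rate ratio 0.80, overdispersion 3.0, one-sided alpha 0.025, power 80%. For Poisson regression with equal arms:

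N = 3.0 × (1.960 × √4 + 0.842 × √4.5)² / (3.7 × (ln 0.80)²) = 3.0 × 32.55 / (3.7 × 0.0498) ≈ 530.

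Taking 10% attrition per year as 30% in all, 530 / 0.70 ≈ 758, close to the stated 750. The fix leaves this unchanged.

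**Illustrative simulation.** There were 691 participants (the number randomized) and 300 replicates per setting. A gamma frailty with variance v = (3.0 − 1)/3.7 = 0.54 gives a placebo variance-to-mean ratio of 3. Everyone is followed for three years, so power is higher than planned and only the comparison between columns matters.

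- Year-1 count: Poisson, with mean frailty × 0.80 (xylitol) or 1 (placebo) × 3.7/3.
- Follow-up care: P₁ = P₀ + g × ln(1 + year-1 count) + noise (SD 0.5), with P₀ a standard normal baseline value.
- Count in years 2 and 3: Poisson, with twice the year-1 mean × exp(d × centred P₁). Here d = 0 means that care has no effect, and d = −0.1 that it protects.

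The values of g and d are assumptions; the documents give none. One year-1 lesion raises care by g × ln 2, which is 0.35, 0.69 or 1.39 baseline SDs for g = 0.5, 1 or 2.

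| g | d | RR, power: baseline covariate | RR, power: follow-up covariate |
|---|---|---|---|
| 0 | 0 | 0.797, 0.897 | 0.797, 0.903 |
| 0 | −0.1 | 0.798, 0.887 | 0.798, 0.897 |
| 0.5 | 0 | 0.802, 0.883 | 0.809, 0.877 |
| 0.5 | −0.1 | 0.804, 0.860 | 0.807, 0.847 |
| 1 | 0 | 0.796, 0.893 | 0.817, 0.840 |
| 1 | −0.1 | 0.808, 0.883 | 0.823, 0.857 |
| 2 | 0 | 0.801, 0.903 | 0.851, 0.757 |
| 2 | −0.1 | 0.812, 0.897 | 0.854, 0.713 |

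Share of the effect (1 − RR) lost, with d = 0:

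- g = 0.5: (0.809 − 0.802)/0.198 ≈ 4%
- g = 1: (0.817 − 0.796)/0.204 ≈ 10%
- g = 2: (0.851 − 0.801)/0.199 ≈ 25%

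The loss appears even when care has no effect on caries, because follow-up care then acts as a proxy for the outcome.

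**Under no treatment effect** (RR 1.0), the follow-up covariate gave estimates of 0.991 to 1.002 and one-sided rejection rates of 0.013 to 0.037. With 300 replicates the standard error around 0.025 is √(0.025 × 0.975/300) = 0.009, so these rates are compatible with the nominal level.

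**A second simulation** used 346 per arm, 80 replicates, and log-slopes of 0.15 to 0.3 per lesion. It gave unadjusted and adjusted rate ratios of 0.802/0.808, 0.808/0.834 and 0.791/0.825. The largest loss is 0.034/0.209 ≈ 16%.

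**The case against.** The strongest reply is that the article never says follow-up values enter the model. Baseline fluoride exposure could be the source of the preventive term. The Missing Data section expects complete baseline measures and gaps only at examination visits, and makes no provision for a covariate built from quarterly calls. That fits baseline covariates. Quarterly questions also serve other purposes, and the exact definition of a named covariate is often left to the analysis plan. This stands to the extent that post-randomization adjustment is likely on the wording but not demonstrated. It does not remove the point. The article itself fixes the covariate list and anchors one item to baseline but not this one. The only preventive-care data that it describes are collected later.

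A reader might also infer that oral hygiene is affected in the same way. The documents do not support this: hygiene behaviors are in the baseline list, and no follow-up collection is described.

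The causal link is also softer than it may look. The Background only reports a suggestion. Under Study Population, every participant has a cavitated lesion at screening or recorded in the past 12 months, so all are caries active at entry. Nothing in the article says that each further lesion brings more care. That objection stands, and for that reason the sizes above are illustrative only.

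**Conclusion.** The point holds for the preventive-regimen covariate. As worded, the primary model may condition on a variable that responds to new caries. If it does, a true benefit is likely to be understated: a rate ratio of 0.80 becomes about 0.81 to 0.85. The upper end, with power falling from about 0.90 to 0.71 to 0.76, needs the strongest link tried. Under weak links the shift is 0.01 or less. All of this rests on assumed links between lesions and care.

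A reader might infer that the plan invalidates the randomized comparison or risks a false claim of benefit. The documents and the check do not support that. Use of follow-up values is not established, the bias found is toward the null, and no type I error inflation was visible in the scenarios tried.

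**What to change.** Add one sentence to Primary Outcome Analysis: the preventive-regimen covariate, like every covariate in the primary model, is its baseline value, for example the baseline fluoride exposure already collected. Say the same of oral hygiene for completeness. Move preventive care received during follow-up to a labelled sensitivity or mediation analysis.

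The cost is a little explained variance. In the simulation with no link from caries to care (g = 0), the baseline covariate gave power of 0.897 against 0.903, and 0.887 against 0.897, for the follow-up covariate. Sample size, alpha and data collection do not change.

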### Study Population

Principal inclusion criteria were age 21-80 and the presence of at least one coronal or root surface cavitated caries lesion (either present at screening or documented in the dental record within the past 12 months). The caries criterion was designed to include participants who were at risk of forming new lesions. Similarly, to ensure an adequate quantity of surfaces at risk, participants were required to have a minimum of 12 teeth with exposed coronal or root surfaces. In addition, participants had to be able to read and comprehend study materials in English, and be able to give informed consent. Exclusion criteria consisted of having more than 10 teeth with caries lesions, having Type IV periodontitis, receiving long-term antibiotic therapy, needing antibiotic prophylaxis prior to dental treatment, having history of head and neck radiation therapy, a history of adverse reaction to either placebo or intervention agent, a serious illness that would interfere with participation, plans to leave the area within the next three years, no telephone, a member of the household already enrolled in the trial, or investigator option.

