### Study Outcomes

#### Primary Outcome Variable

The primary study outcome is the cumulative D_2 _or Filled Surface (D_2 _FS) increment (root and coronal surfaces combined) cumulated from baseline through the three follow-up examinations. Use of the cumulative, combined D_2 _FS increment measure allows comparison with existing literature and increases confidence that any effect detected represents the prevention cavitation, which has substantial clinical implications for individuals who experience it.

The D_2 _FS increment is computed as the weighted sum, across tooth surfaces, of changes in surface status associated with 64 pre-defined transitions in tooth-surface integrity (Table 1). Our weighting scheme assigned a range of -1, 0, or +1, with transitions to a worse status receiving positive weights and transitions (reversals) to a better status receiving negative weights. No reversals are considered valid for the D_2_FS increment. A transition that reflects no change (e.g., F to F), a change from D_2 _to treated status (F or C), or to or from an unscorable status (Y or M) is scored 0 and hence effectively excluded from analysis. A transition from sound (S) to crowned (C) is given a score of 0 to minimize the influence of non-caries-related treatment on increment counts. Transition from S to CD_2 _is considered implausible given annual examinations. After completion of bootstrapping analyses of a caries increment dataset from another study, we concluded that the optimal way to handle unlikely or implausible transitions is to ignore them (i.e., assign a weight of zero). Hence for our primary analysis the bolded cells in Table 1 will be ignored, although they will be included in an outcome in planned secondary analyses.

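### The primary model leaves out the baseline number of tooth surfaces at risk, an available covariate that may modestly improve precision

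*Protocol article*

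**What the plan says.** Under Primary Outcome Variable, the D2FS "increment is computed as the weighted sum, across tooth surfaces, of changes in surface status". A transition "to or from an unscorable status (Y or M) is scored 0 and hence effectively excluded from analysis".

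Under Primary Outcome Analysis, a negative binomial model contains treatment and clinical centre. It states in advance that the "covariates are age and age-squared, intensity of preventive regimen, oral hygiene behavior measures, and severity of baseline caries". The last of these is a count of decay, "which is defined as the sum of decayed surfaces at the baseline examination". Log person-years enters "as an offset to adjust for length of time since the participant was randomized". The model is also written as an equation, and neither the list nor the equation has a term for teeth or surfaces at risk.

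Under Study Population, "participants were required to have a minimum of 12 teeth with exposed coronal or root surfaces", and the stated reason is to have enough surfaces at risk. No upper limit is given. According to Caries Examination and Randomization and Treatment Contacts, each surface is coded individually, and a caries examination takes place at the baseline visit before allocation.

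**The concern.** Other things equal, a participant with more surfaces that can develop a lesion has more chances to add to the count. The eligibility rule shows that the authors regard this quantity as relevant, and the data to compute it are already collected. The planned severity covariate measures something else: it counts surfaces already decayed.

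If increments rise with the number of surfaces at risk, that predictable variation stays in the negative binomial dispersion and widens the standard error of the treatment effect. The trial randomized 691 against a target of 750, so precision available at almost no cost is worth having.

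**Working it through.** **1. The plan's own figure.** Inputs from Sample Size: placebo increment 3.7 (within the stated 2.3 to 4.9), 20% reduction, overdispersion 3.0, one-sided alpha 0.025, power 80%, attrition 10% per year. The Poisson regression formula for a 1:1 binary covariate is

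N = φ(z_α√V0 + z_β√V1)² / (μ0 b²), with V0 = 4, V1 = 2 + 2/0.8 = 4.5, b = ln 0.8 = -0.2231.

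N = 3 × (1.960 × 2 + 0.8416 × 2.1213)² / (3.7 × 0.04979) = 97.65 / 0.1842 = 530.03, so 531. Dividing 530.03 by 0.9³ = 0.729 gives 728; dividing by 0.70 gives 758. Both are within 3% of 750, so the assumed mean and overdispersion are a fair base for what follows.

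**2. Range that eligibility permits.** Caries Examination gives 5 coronal + 4 root = 9 surfaces for anterior teeth. Assume 9 for every tooth and a full dentition of 28 or 32 teeth. Then 12 × 9 = 108 surfaces compares with 28 × 9 = 252 or 32 × 9 = 288, a ratio of 2.3 or 2.7. These are extremes, not an observed spread.

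**3. Which surfaces are at risk at the start.** In Table 1, only the rows for S/P/D1/PD1, F/FD1 and C/CD1 contain a +1. These define the surfaces at risk in the first interval.

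**4. Gain from adjustment.** Simulation, 400 trials per setting: 691 × 0.729 = 504 completers, placebo mean 3.7, rate ratio 0.8, total dispersion k = (3.0 - 1)/3.7 = 0.54. Number of teeth stands in for surfaces, and the tooth distributions are assumed. No other covariates are in these models. Each entry is the mean squared standard error of the log rate ratio relative to the model without a tooth term.

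| Teeth (assumed) | Increment and teeth | ln(teeth) as covariate | ln(teeth) as offset |
|---|---|---|---|
| Triangular 12-28, mode 26 | proportional | 0.970 | 0.969 |
| | square root | 0.992 | 1.005 |
| | unrelated | 1.001 | 1.049 |
| Uniform 12-28 | proportional | 0.928 | 0.927 |
| | square root | 0.982 | 1.015 |
| | unrelated | 1.001 | 1.106 |
| Uniform 12-32 | proportional | 0.909 | 0.908 |
| | square root | 0.977 | 1.018 |
| | unrelated | 1.001 | 1.134 |

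**5. In terms of power.** Simulated power has a Monte Carlo error of about √(0.8 × 0.2/400) = 2 points, so the variance ratio r is converted instead: power = Φ(2.8016/√r - 1.960), starting from 80%. For r = 0.970, 0.928 and 0.909 this gives about 81%, 83% and 84%. For r = 0.977, the largest square-root gain, it gives 80.9%. In participants, 691 × 0.030 = 21 to 691 × 0.091 = 63.

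**6. Sensitivity to the spread.** A closed-form approximation gives 2.0% for a mostly complete dentition (mean 25 teeth, SD 3) under proportionality, or 80.8% power. This approximation runs above the simulation (4.7% against 3.0% for the triangular case). For an artificial sample split between 12-15 and 25-28 teeth it gives 17.9%. The 3-9% range is therefore illustrative, not a bound.

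**7. Overlap with age.** In a separate simulation (691 participants, uniform 12-28 teeth, 60-100% of surfaces exposed, proportional increments, age and age-squared in both models), adjustment lowered the standard error by 4.9%. With tooth count made to decline with age (latent correlation -0.5), it lowered it by 4.2%. Overlap with baseline decay was not tested.

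**The case against.** The strongest reply is that nothing here is invalid. Randomization balances surfaces at risk in expectation, the estimand is a per-person rate, the model matches it, and several prognostic covariates are already listed. The gain rests on a tooth distribution and a relation that the documents do not supply, and it may be close to zero. All of this stands. It limits the point to efficiency and rules out saying that precision is certainly lost. It does not remove the point: the article fixes its covariate list and model equation in advance, so this is not detail left to an unseen analysis plan, and the covariate costs almost nothing if it proves unrelated.

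A reader might infer more from the text in two places.

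- **That surfaces decayed or unscorable at baseline can never score.** They can. The outcome cumulates over three follow-up examinations. With intervals scored in turn, Table 1 gives D2 to F = 0 and then F to FD2 = +1, and Y to S = 0 and then S to D2 = +1. A baseline FD2 surface can likewise go to F and back to FD2.
- **That "hence effectively excluded from analysis" conflicts with a person-time offset.** It does not. Such a transition adds nothing to the sum. The text does not claim to remove anything from a denominator, and the per-person rate has no surface denominator.

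**Conclusion.** The point holds as a modest, optional gain in efficiency. The primary model has no term for baseline surfaces at risk, although the outcome is a sum over surfaces and the count is available before randomization.

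Under the three tooth distributions simulated, adjustment reduces the variance of the log rate ratio by about 3-9% if increments are proportional to surfaces, about 1-2% under a square-root relation, and not at all if unrelated. In a design with 80% power, these are gains of roughly 1 to 4 points, under 1 point, and none. A narrower spread of teeth, or overlap with age and baseline decay, would reduce them.

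The planned test is neither biased nor invalid. A reader might also infer that the covariate would make up the shortfall of 59 participants. Only the widest assumed spread under proportionality reaches that (about 63); the narrowest of the three gives about 21.

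**What to change.** Under Primary Outcome Analysis, before unblinding, add to the pre-specified covariates the natural log of the number of baseline surfaces called S/P/D1/PD1, F/FD1 or C/CD1. Describe it as surfaces at risk at the start of follow-up, not as the only surfaces that can ever score.

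Enter it as a covariate and keep log person-years as the offset. A forced surface offset raised the variance by about 5-13% in the simulations with no relation, whereas the covariate left it essentially unchanged.

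The cost is one degree of freedom and one derived variable, with no new data collection. Making the change before unblinding avoids the appearance of a data-driven choice.
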